##### Intervention

The intervention will consist of a series of counseling and participatory workshops, planned based on the unique practice identified in Phase I. On the day of enrollment, women in the intervention arm will receive dual-method counseling with a tool developed based on the practice identified in Phase I, in addition to regular family planning counseling with an existing counseling tool [36]. The dual-method counseling will be conducted for 20–40 min by trained research assistants.

Two weeks after enrollment, women in the intervention arm will be invited for a 1-day participatory learning workshop (5 h) at the same health facilities where they were recruited. Women may decide whether to participate. The workshop will be facilitated by research assistants and positive deviants, using a training protocol developed after Phase I. It will include simulations and role-plays for successful communication about using a condom with their partners and a group discussion regarding family planning and HIV/STI risk.

Bi-monthly telephone counseling will be provided by positive deviants three times (3, 5, and 7 months after enrollment). Each counseling session will take 10–20 min and aim to remind women of the risk of unintended pregnancies and HIV/STIs and strengthen their capacity to communicate using a condom with their partners. The 2-month intervals can allow women to reflect on counseling messages, discuss the use of condoms with their partners, and put it into practice. Positive deviants, therefore, can provide more effective counseling tailored to participants’ individual needs through understanding their situation.

Women in the control group will be provided regular family planning counseling including dual-method use for 10–30 min by trained research assistants using the same existing tool on the day of enrollment [36]. Moreover, refresher training will be provided bi-monthly on family planning and HIV/STI risk via phone, by research assistants three times (3, 5, and 7 months after the enrollment).

Condoms will be provided for free, regardless of the allocation at the selected health facilities. Before the intervention starts, the research assistants will receive a 2-day training session about the contents of the existing counseling tool by health professionals [36].

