##### Outcomes

The primary outcome is dual-method use. In this study, dual-method use is defined as the use of male or female condoms along with HECs such as pills, injectables, implants, male and female sterilization, and IUD consistently in the last 2 months, before each follow-up interview [8]. The outcome measure combines two questions regarding the frequency of condom use and HEC use. The frequency of condom use will be asked with an item: “How often did you and your partner use a male or female condom during the past 2 months?” Women will answer this question using a four-point scale “every time,” “almost every time,” “sometimes,” and “never.” Only those who answered “every time” will be considered as having consistent condom use. Women will also be asked if they have been using any HECs with a question, “Apart from condoms, have you been using any other forms of protection against pregnancy during the past two months?” Responses to these two questions will be used to construct the dual-method use outcome with the following categories: (1) dual-method use (consistent condom and HEC use); (2) inconsistent use of condoms and HECs; and (3) single or no use of contraceptive methods.

The secondary outcome is the self-reported first occurrence of pregnancy and STIs in the previous 2 months [37]. They will be assessed with the following two questions: “Have you been told by a healthcare provider that you got pregnant for the first time in the past 2 months?” and “Have you been told by a healthcare provider that you had any STIs such as chlamydia, gonorrhea, or trichomonas infection for the first time in the past 2 months?”

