##### Data collection

On the day of enrollment, all women will be interviewed using a pretested structured questionnaire to identify basic baseline characteristics. They will then be followed up via phone bi-monthly for 8 months to assess how the intervention influences dual-method use and pregnancy and STI incidence (2, 4, 6, and 8 months after enrollment). All interviews will be conducted by trained female research assistants using an interview guide in either English or Runyankore. All data will be entered using EpiData version 4.6.

All participants will be given some incentives worth 10,000 UGX (equivalent to US$3) for their time and participation in the study after the initial interviews. Participants who participate in the learning workshop will receive 20,000 UGX (equivalent to US$6) for transportation.

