##### Data analysis

The background characteristics of women will be compared between the intervention and the control group using Pearson’s chi-squared or Fisher’s exact tests [44]. Mixed effects logistic regression analysis will be performed with a random effects term for the clusters to access the effect of the intervention on the following outcomes: dual-method selection and adherence; self-reporting pregnancy; and incidence of STI in the 2 months before each follow-up data collection. In addition, hierarchical logistic regression model will be introduced to ascertain the predictors of each outcome. Model 1 will be adjusted for demographic variables, such as age, education, and the number of children. Model 2 will be adjusted for the status of residence (urban or rural) in addition to demographic variables. Model 3 will include the type of HECs at the baseline sequentially, which is known to be associated with dual-method use [8, 45]. Model 4 will be adjusted for variables related to their partners, such as partner’s attitude toward family planning. Model 5 will include women’s perceived risk of HIV/STIs. Model 6 (full model) will be adjusted for all variables. Besides, sub-group analyses will be conducted among HIV-seroconcordant and -discordant couples. All the analyses will be conducted on both per-protocol and intention-to-treat bases. The per-protocol analysis will assess the efficacy of the intervention while the intention-to-treat analysis will test its effectiveness [46]. Rates of attrition and reasons for dropout will be compared between the intervention and the control groups [47]. The significance level will be set at 5%. STATA version 13.1 will be used for all data analyses.

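### The pregnancy and STI items record only events a healthcare provider told the woman about, yet the results are labelled incidence: events are lost, and for STI the loss could differ by arm

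*Protocol article*

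**What the plan says.** All references are to the Phase II part of the protocol article unless stated otherwise.

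- **Outcomes** defines the secondary outcome: "The secondary outcome is the self-reported first occurrence of pregnancy and STIs in the previous 2 months". It gives both items verbatim. The STI item is "Have you been told by a healthcare provider that you had any STIs such as chlamydia, gonorrhea, or trichomonas infection", and the pregnancy item is "Have you been told by a healthcare provider that you got pregnant for the first time in the past 2 months".
- **Data collection** sets the mode of follow-up: "They will then be followed up via phone bi-monthly for 8 months", at months 2, 4, 6 and 8. The stated purpose is "to assess how the intervention influences dual-method use and pregnancy and STI incidence". The article describes no scheduled pregnancy or STI test.
- **Data analysis** models the two outcomes by mixed effects logistic regression as "self-reporting pregnancy; and incidence of STI in the 2 months before each follow-up data collection". Here only STI carries the word incidence; pregnancy is called self-reported.
- **Intervention** gives the intervention arm an extra 20–40 minutes of dual-method counseling at enrollment. Two weeks later these women are "invited for a 1-day participatory learning workshop (5 h) at the same health facilities where they were recruited". Attendance is voluntary, the facilitators are research assistants and positive deviants, and the content includes a group discussion of HIV/STI risk. Both arms receive three phone sessions, at months 3, 5 and 7. The control sessions also cover family planning and HIV/STI risk.
- **Discussion**, in its limitations, names social desirability as a reason why STIs and unintended pregnancies may be under-reported, and offers assurance of confidentiality as the remedy.

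**The concern.** A yes to either item needs four things: the event happened, the woman saw a provider, the provider recognised it, and she was told. An infection that was never tested for is scored as no event. So is a pregnancy she knows of from a home test or missed periods, and one that ended before any clinic visit. The quantity recorded is incidence multiplied by the chance of diagnosis and notification, so the label incidence claims more than the items deliver.

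Two consequences follow. If the chance of diagnosis is the same in both arms, the trial loses events and precision. If it differs, the contrast between arms mixes an effect on infection with an effect on being diagnosed. For STI there is a possible route to a difference, because one arm gets more STI-risk content and an invitation back to the facility. Assuring confidentiality cannot recover an event that the woman was never told about, so the limitation as written addresses a different problem. Pregnancy and STI are the health consequences that motivate dual-method use, so a null or adverse result on them would need to be interpretable.

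**Working it through.** The plan gives no event rate, effect size or power for pregnancy or STI, so there is no figure of its own to reproduce. Every risk, detection probability and true ratio below is an assumption.

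**Inputs from the protocol** (sample-size section of Phase II): 960 women, 26% dropout, 20 facilities, ICC 0.006, 5% significance level (taken as two-sided).

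**1. Model.** Let d be the probability that a true event is diagnosed and the woman told. Then

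observed risk = true risk × d, and observed RR = true RR × k, where k = d(intervention) / d(control).

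For rare events the odds ratio from the logistic model is close to this risk ratio.

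**2. Equal detection (k = 1).** The ratio is unchanged. The cost is in events and power.

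- Women followed per arm: 960 × 0.74 / 2 = 355.2, or 35.5 per facility.
- Design effect: 1 + (35.52 − 1) × 0.006 = 1.207. Effective number per arm: 355.2 / 1.207 = 294.
- Events, with an assumed 6% control risk: 355 × 0.06 = 21.3 true events. At 80% detection 21.3 × 0.8 = 17.0 are recorded; at 30%, 21.3 × 0.3 = 6.4.
- Power, comparing two proportions with 294 per arm:

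| Assumed true risks (control, intervention) | Power, all events detected | Power, 30% detected in both arms |
|---|---|---|
| 5%, 2.5% | 35.8% | 13.6% |
| 10%, 5% | 63.5% | 23.1% |
| 20%, 10% | 92.7% | 41.9% |

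**3. Unequal detection.** A true benefit disappears when k = 1 / RR:

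| True RR | k that hides it | Example |
|---|---|---|
| 0.5 | 2.00 | 30% vs 60% detected |
| 0.7 | 1.43 | 30% vs 42.9% |
| 0.8 | 1.25 | 30% vs 37.5% |
| 0.9 | 1.11 | 30% vs 33.3% |

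For a true RR of 0.70, the observed ratio is 0.70 × 1.10 = 0.77, 0.70 × 1.25 = 0.88, 0.70 × 1.43 = 1.00 and 0.70 × 1.60 = 1.12. With no true effect, k = 1.25 gives 1.25. The formula works in the other direction too: k = 0.80 turns a true 1.00 into 0.80, and a true 0.70 into 0.56.

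**4. Can k be learned from what is described?** The two quoted items do not reveal d in either arm, so they cannot separate a change in infection from a change in diagnosis.

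**The case against.** The strongest case against has five parts.

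*The items still measure incidence.* A reader might infer that they capture care-seeking and testing instead of incidence. That goes too far. They capture incidence scaled by detection, and with equal detection the ratio between arms is sound. This objection stands.

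*The arms differ less than they seem to.* A reader might infer that the intervention's clinic contact and STI counseling will hide or reverse a real benefit. The protocol does not support that. Controls hear about HIV/STI risk by phone in the same three months. The extra contact is one optional workshop with no healthcare provider named as facilitator, and no testing, examination or referral is described. Social-desirability under-reporting could also be stronger in the more intensively counseled arm and push the other way. This stands: a difference in detection is possible, but it is neither shown nor excluded.

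*Pregnancy is different.* The Data analysis section calls it self-reported, and nothing suggests that pregnancy diagnosis would differ by arm. This stands. For pregnancy the problem is the needless loss of events that a woman could report directly, together with the incidence label in Data collection.

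*The full interview guide is not shown.* It may contain questions on visits or testing, so one cannot say that nothing of the kind is asked. This stands too. It does not alter the outcome definitions, which the article gives verbatim and which use only the provider's notification.

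*Testing happens after randomization.* It would be tempting to read the STI contrast as an effect on infection only when testing is similar between arms. That rule would be wrong. If condom use prevents infection, fewer women have symptoms and fewer are tested, so testing could fall because the intervention works. Equal testing rates would not guarantee equal detection either. The fix therefore contains no such rule.

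**Conclusion.** The point holds as a mismatch between measure and label, with an avoidable loss of information. Both items count only events that a provider communicated, and the results are called incidence: for both outcomes in Data collection, and for STI in Data analysis. With equal detection the cost is precision alone. At an assumed 30% detection, power for a halving of risk falls to well under half its full-detection value across assumed control risks of 5% to 20%. For STI, unequal detection could shift the ratio either way. The ratio needed to hide a benefit is 1/RR, so a modest true effect is fragile (1.25 for RR 0.8) and a large one is not (2.00 for RR 0.5). The protocol supplies no detection rates, so the actual size and direction are unknown, and the calculations show sensitivity only. The power figures also assume that the sample-size ICC applies to these outcomes. The limitation on social desirability does not cover undiagnosed events. Only secondary outcomes are concerned; dual-method use, on which the trial was sized, does not depend on these items.

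**What to change.** 1. **Pregnancy item (Outcomes).** Ask directly whether the woman is pregnant or has been pregnant at any time since the last interview, including pregnancies that have ended. Then ask whether a provider or a test confirmed it. Analyse any reported pregnancy, with confirmed pregnancy as a sensitivity analysis.
2. **STI item (Outcomes).** Keep the diagnosis question. Add a question, in both arms, on whether she was examined or tested for an STI since the last interview.
3. **Labels (Data collection, Data analysis).** Call the outcome *provider-diagnosed STI* instead of STI incidence.
4. **Reporting (Data analysis).** Report testing by arm descriptively. Add a simple sensitivity analysis that divides the observed ratio and its confidence limits by a range of detection ratios k on both sides of 1. For example, an observed 0.88 with k = 1.25 corresponds to 0.88 / 1.25 = 0.70. Do not make interpretation conditional on similar testing.
5. **Limitations (Discussion).** State that undiagnosed events are not captured and that STI detection may differ between arms.

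The cost is small: reworded or added questions at the four existing phone interviews, one descriptive table and one short sensitivity analysis, with no extra visits, staff or tests. Unconfirmed pregnancy reports are slightly less specific, which the confirmed-only analysis addresses. The questions must be in place during follow-up, because testing that is not asked about then would be hard to recover later.

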##### Other information

The following information will be collected during the baseline interviews to conduct sub-group analyses and to identify factors associated with the use of condoms: age; education; employment; area of residence (rural or urban); reproductive history; pregnancy intention; sexual history; STI history; substance use; domestic violence; contraceptive methods in use; awareness of dual-method use; spousal communication on family planning; HIV status of participants and their partners; disclosure of HIV status; antiretroviral therapy (ART) treatment status [14, 22, 38]; HIV-related knowledge (HIV-KQ-18) [39]; perceived STI and HIV infection risk [40]; condom use self-efficacy [41]; sexual relationship control power (the Sexual Relationship Power Scale [SRPS]) [42]; and women’s perception of the social acceptability of contraception [43].

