##### Data collection

The five female trained research assistants will conduct face-to-face interviews using a pretested structured questionnaire with the participants. These interviews aim to identify women practicing dual-method use and their basic sociodemographic characteristics. Data collection items include basic sociodemographic characteristics, the types of HECs, the frequency of condom use in the past 2 months, and the histories of unintended pregnancies and diagnosed HIV/STIs. Women using both HECs and condom always will be regarded as practicing dual-method use. Dual-method users without no reported histories of unintended pregnancies and HIV/STIs will be considered as positive deviants.

Next, in-depth interviews will be conducted by the research assistants with all positive deviants to identify their unique practice, such as effective communication for use of condoms that is actually working. Then, 10 women who do not practice dual-method use will be randomly selected for in-depth interviews to document common practices and verify if the practice identified in positive deviants is unique. The interviews will be open-ended and an interview guide will be used. The interview guide focuses on the following domains: (1) perceptions of condom use and contraception; (2) reasons and motivations for condom use or non-use; (3) negotiation and communication for condom use; and (4) risk perceptions for or unintended pregnancy and HIV/STIs.

The data collection tools were first developed in English and then translated to Runyankore by an independent researcher. They were back-translated to English by the Ugandan researcher (SM) to ensure the accuracy of the translation. All interviews will be conducted in either English or Runyankore. In-depth interviews will be audio recorded based on the consent of participants. All participants will be given some commodities worth 10,000 Ugandan Shillings (UGX) (equivalent to US$3) after the initial interview; those who participate in the in-depth interview will receive 10,000 UGX for their time and transportation.

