#### Phase II: cluster randomized controlled trial

##### Sample, eligibility, and recruitment

The minimum required sample size for this trial is 588. It was calculated based on data from research on the effect of case management and peer education program on the uptake of dual- method use in the USA (odds ratio [OR] = 1.58, 95% confidence interval [CI] = 1.03–2.43) [32]. The less conservative effect size of 2.43 was used because this trial will include only women who have already used HECs, unlike the prior research which recruited adolescent girls regardless of their contraceptive use [32]. Then, an intraclass correlation coefficient (ICC) of 0.006 was considered [33, 34]. The ICC was adapted from a clinic-based condom use intervention in SSA [33]. The required minimum sample size was 760 after considering the ICC. Considering a 26% dropout rate, 960 participants will be recruited (480 participants in each arm) [22]. The power of the study was set at 80% and the significance level was set at 5%. Open Epi version 3 was used for the calculation.

Twenty health facilities will be purposively selected considering the size and rural/urban status. The same inclusion criteria as Phase I will be used for this intervention study, but if women have been practicing dual-method use in the 2 months before recruitment, they will be excluded. The same sampling method as Phase I will be used to recruit women at health facilities. Eighty women will be recruited from each of the hospitals and county-level health centers, and 40 from each of the sub-county-level health centers and parish-level health centers.

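### Women with different starting levels of condom use enter Phase II together, but graded condom frequency is not named as a baseline item or as a covariate of the intervention-effect model

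*Protocol article*

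**What the plan says.** All statements are in the protocol article.

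- **Entry (Phase II, Sample, eligibility, and recruitment).** Every woman must be using a highly effective contraceptive (HEC), and "if women have been practicing dual-method use in the 2 months before recruitment, they will be excluded".
- **Outcome (Phase II, Outcomes).** Dual-method use means an HEC plus condoms used "consistently in the last 2 months, before each follow-up interview". On the wording of the condom question the section says: "The frequency of condom use will be asked with an item". The answer has four levels, and only the top one, *every time*, counts as consistent. Inconsistent condom users form their own middle category of the outcome.
- **Phase II baseline (Other information).** The list opens "The following information will be collected during the baseline interviews to conduct sub-group analyses and to identify factors associated with the use of condoms". The nearest entries are "sexual history; STI history; substance use; domestic violence", "contraceptive methods in use; awareness of dual-method use; spousal communication on family planning" and condom use self-efficacy. Condom frequency is not named.
- **Phase I (Data collection).** Here the data items do include "the frequency of condom use in the past 2 months".
- **Models (Phase II, Data analysis).** The intervention effect is estimated by mixed effects logistic regression with a random effect for clusters; no covariate is named. Models 1 to 5, introduced separately to find predictors, name demographics, residence, HEC type, partner variables and perceived risk. Model 6 takes all variables. On partners: "Model 4 will be adjusted for variables related to their partners", with the partner's attitude toward family planning as the example.

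**The concern.** All entrants use an HEC, so the exclusion turns on condom use. It removes consistent users and leaves three groups that start at different distances from success. A woman at *almost every time* needs a smaller change than one at *never* to be counted as a dual-method user.

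The plan treats partial use as a distinct state at follow-up but names no counterpart at entry. It brings HEC type into a model because of its known association with dual-method use; the same reasoning would favour the behaviour from which the outcome is built. With 10 facilities per arm, the share of partial users could differ between arms by chance or through recruitment. If the graded value is not in the analysis, such a difference is not corrected, and whatever precision it could bring is lost.

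**Working it through.** The point disputes no figure in the plan. The documents give neither the baseline mix of condom use nor the uptake at each level, so every mix and uptake below is an **assumption**.

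**1. Design inputs from the plan.** 960 women, 20 facilities, 480 per arm, ICC 0.006, target odds ratio 2.43, dropout 26%. Mean facility size is 960/20 = 48, so the design effect is 1 + 47 × 0.006 = 1.282. As a check, 588 × 1.282 = 754, close to the stated 760.

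**2. Chance imbalance in partial users.** Assume 30% of entrants use condoms at least sometimes, with follow-up dual use of 25% in them and 5% in never-users. The rate with no true effect is 0.3 × 0.25 + 0.7 × 0.05 = 0.11.

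SD of the arm difference in the partial-user share = √[2 × 0.3 × 0.7/480 × (1 + 47 × ICC)].

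| ICC of baseline condom use | SD | 95% range | × (0.25 − 0.05) = shift in outcome difference |
|---|---|---|---|
| 0.006 (the plan's ICC) | 0.0335 | ±6.6 points | ±1.3 points |
| 0.05 (assumed) | 0.0541 | ±10.6 points | ±2.1 points |

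The recruitment quotas of 80 or 40 women imply 4 large and 16 small facilities (4 × 80 + 16 × 40 = 960). The size-weighted mean is (4 × 80² + 16 × 40²)/960 = 53.3, which moves ±10.6 to about ±11.0.

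**3. Those shifts in proportion.** At 11% and ICC 0.006, the whole 95% sampling range of the arm difference is 1.96 × √(2 × 0.11 × 0.89/480 × 1.282) = ±4.5 points. The ±1.3 points are part of it: 0.0131²/0.0448² = 0.086, about 9% of the variance. An odds ratio of 2.43 on 11% gives 0.11 × 2.43/(0.89 + 0.11 × 2.43) = 0.231, a 12.1-point effect. The 95% shifts are therefore 1.3/12.1 = 11% and 2.1/12.1 = 17% of the targeted effect.

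**4. A finer mix.** Assume 70% never, 22% sometimes, 8% almost every time, and control uptake by level of 3/8/20% (weakly prognostic) or 2/10/45% (strongly prognostic). The overall control rates are 5.46% and 7.2%. These lie nearer than 11% to what the sample size suggests: a two-proportion formula with an assumed 5% control rate and odds ratio 2.43 gives 584, against the stated 588.

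Move 5 points from *never* to *almost every time* in one arm, with no true effect:

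- Weak: 0.0546 + 0.05 × 0.17 = 0.0631; apparent odds ratio 1.17.
- Strong: 0.072 + 0.05 × 0.43 = 0.0935; apparent odds ratio 1.33.

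With an 8% share and 480 per arm, the chance of an imbalance above 5 points is 0.01 at ICC 0.006 and 0.12 at ICC 0.05. With a 15% share it is 0.06 and 0.24.

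**5. Power with and without adjustment.** Simulation: 20 facilities of 36 analysed women (960 × 0.74/20 ≈ 36), outcome ICC 0.006, true odds ratio 2.43 within baseline level, 600 runs per scenario. The test is a logistic GEE with bias-reduced standard errors and 18 degrees of freedom, standing in for the planned mixed model. Monte Carlo error is about 0.02.

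| Uptake gradient | ICC of baseline mix | Unadjusted | Adjusted |
|---|---|---|---|
| Weak | 0.006 | 0.74 | 0.76 |
| Weak | 0.05 | 0.74 | 0.77 |
| Strong | 0.006 | 0.63 | 0.74 |
| Strong | 0.05 | 0.53 | 0.75 |

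**The case against.** The case against a heavier charge is good, and most of it stands.

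- **A reader might infer that condom frequency is asked only to exclude dual users and then discarded.** The article does not say so. It states the exclusion, not how the question is put or whether the answer is kept. The list in question is headed Other information and follows the outcome items, sexual history is an open heading that could hold the item, and the SPIRIT schedule figure is not available here. What stands is that the item is not named where baseline data are listed, although Phase I names it.
- **A reader might infer that the baseline of the primary outcome goes unadjusted.** The binary outcome is 0 for every entrant by exclusion, so it has no baseline variation. The gap concerns the graded component behind it.
- **A reader might infer bias.** Chance imbalance in a randomized trial is not bias and is already reflected in the standard error. A recruitment difference is possible, since arm-specific counseling begins on the day of enrollment, but nothing in the article shows one.
- **Covariates may be left to an analysis plan, and Model 6 takes all variables.** True in part. But Model 6 can use only what is recorded, and Models 1 to 6 are presented as predictor models, apart from the intervention-effect model.
- **The strong scenario is steep.** Uptake of 45% against 2% is assumed, and the documents do not establish that prior frequency is the strongest predictor. In the weak scenario adjustment gains little.
- **A reader might infer that Model 4 cannot be fitted.** Partner's attitude is only an example there, and the baseline list does contain partner-related items such as spousal communication and partner's HIV status.

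**Conclusion.** The point holds as a worthwhile improvement; it is not a fault that invalidates the analysis. Women at three levels of condom use enter alike, and neither the baseline list nor any model names that level. The unadjusted mixed model remains a valid comparison under randomization. It forgoes precision and leaves chance or recruitment imbalance in partial users uncorrected.

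The size cannot be fixed from the documents. Under the stated assumptions, the loss is 2 to 3 points of power if condom frequency is weakly prognostic and about 12 to 22 points if it is strongly prognostic. The 95% chance shift in the outcome difference is modest beside an effect of the targeted size.

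The partner's-attitude mismatch is minor and does not touch the primary effect estimate.

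**What to change.** 1. State that the four-point condom-frequency item, in the same wording and 2-month window as at follow-up, is recorded at enrollment for every woman and kept as a baseline variable.
2. Tabulate it by arm with the other background characteristics.
3. Prespecify it as a fixed covariate in the mixed logistic model for dual-method use, or say why it is left out.
4. Align the baseline list with Model 4: either list the partner's attitude toward family planning or name a partner variable that is already collected.

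**Cost.** Little or nothing in data collection for condom frequency, because the exclusion already requires asking about it. One covariate in the model, which is two indicator terms if entrants fall in the three lower levels. The adjusted odds ratio is conditional on baseline frequency and will generally differ from the unadjusted one, so the report should say which is primary. For partner's attitude, at most one more baseline question.
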